0.3.3 Prodromal Follow Up Visits

Refer to the PPMI Schedule of Activities for the Prodromal cohort to determine the

activities to be conducted at the follow up visits.

After the Baseline visit is completed, participants will be evaluated in clinic annually and

remotely every 6 months, for a minimum of 5 years of longitudinal follow up visits.

Annual visits are anticipated to take about 6-8 hours (could occur over more than one

day). Options for Remote 6-month visits include virtual visits by video link or

telemedicine, or phone/audio only. The remote 6-month visits will take about 1-2 hours.

Sites should complete as many assessments at the Remote (“R”) visit as is feasible, based

on how the visit is conducted (i.e., videoconference versus in-home or audio only) and

ability to do an assessment.

1

0.3.4 Prodromal – Diagnostic Visit

If a Prodromal participant is clinically diagnosed with PD or other neurodegenerative

disorder during a scheduled visit, study procedures will follow the applicable standard

visit schedule of activities and the visit will be labeled as a Standard visit.

If a Prodromal participant is suspected to have developed PD or is diagnosed with PD or

other neurodegenerative disorder outside the window of a scheduled visit, then the

participant should be contacted to return for an in-person assessment called a diagnostic

visit. This in-person visit should occur within 45 days of the site being aware of the

diagnosis. The Visit Status data form should indicate the type of visit is a “Diagnostic

visit” and should be conducted as outlined below.

1

) Investigator determines participant has diagnosis of PD or other

neurodegenerative disorder.

If at the in-person diagnostic visit the investigator determines that the

participant has a diagnosis of PD or another neurodegenerative disorder, then:

a) If the next planned visit is an annual study visit, this diagnostic visit will

take the place of the next annual visit. The participant will undergo all

assessments scheduled for that annual visit.

•

If not already scheduled as part of that visit, DaTscan imaging

and MRI will be added.

PPMI

Page 25 of 55

Version Date: 01Feb2021

[figure not shown]

[figure not shown]

DocuSign Envelope ID: 706F2DD8-8346-4731-A419-FF8E7C48DF97

b) If the next planned visit is a remote study visit, then that remote visit

will be replaced by this in person diagnostic visit. The following

assessments will be added to those already scheduled as part of the

remote visit:

•

Blood and urine research sample collection.

2

) Investigator determines participant does not have diagnosis of PD or other

neurodegenerative disorder.

If at the in-person diagnostic visit the investigator determines that the

participant does not have a diagnosis of PD or another neurodegenerative

disorder, then no further study assessments should be conducted. This visit

will not take the place of an annual or remote visit, rather will be labeled as

an Unscheduled visit. Ensure the Visit Status data form indicates the type

of visit is a “Diagnostic visit”. Resume the participant’s regular visit

schedule.

1

0.4 Need for PD Therapy Visit

The need for PD therapy may be identified in the following ways:

1

2

3

) Participants may identify the need for PD therapy and start treatment outside of a

study visit.

) Participants may identify or confirm the need for PD therapy and start treatment at a

study visit.

) Participants may identify the need for PD therapy at a study visit, but start treatment

following the study visit.

If a PD participant or a prodromal participant identify the need for PD medication at an in-

person visit, the visit will follow the schedule of activities for that visit. Ensure the Visit

Status data form indicates the type of visit is a “Need for PD Therapy visit”. Resume the

participant’s regular visit schedule following that visit.

If the site becomes aware that a participant will begin PD medication outside of a scheduled

in person visit, the site should determine if the participant is willing to return to conduct an

in person visit prior to starting PD medications. If a participant is unwilling or unable to

return for an in person visit prior to starting PD medication, conduct the next study visit per

the regular visit schedule (participant should arrive at visit holding medication). If the

participant agrees, schedule an in-person visit as soon as possible following the participant’s

decision to request medication. The visit for starting PD medication assessments will follow

the schedule of activities of the next planned in-person visit. Ensure the Visit Status data

form indicates the type of visit is a “Need for PD Therapy visit”. Resume the participant’s

regular visit schedule following that visit.

If a participant begins PD medications following the completed need for therapy visit, the

site will communicate by phone with the participant to obtain and record the medication dose

and start date.

PPMI

Page 26 of 55

Version Date: 01Feb2021

[figure not shown]

[figure not shown]

DocuSign Envelope ID: 706F2DD8-8346-4731-A419-FF8E7C48DF97

1

0.5 Premature Withdrawal Visit

If a participant withdraws from the study during a scheduled annual visit, proceed with the

visit as outlined. Ensure the Visit Status data form indicates the type of visit is a “Premature

Withdrawal visit”.

If a participant withdraws from the study outside of a scheduled annual visit and agrees to be

seen for one more visit, the next scheduled annual visit should be completed. Study

procedures will be the same as outlined in the schedule of activities for that respective annual

visit, except for the activities as outlined below. Alternatively, if the participant is unwilling

or unable to return for a final in person visit, the premature withdrawal visit could be

completed by video link or telemedicine. In addition to completing the activities outlined in

the schedule of activities, the site will complete the Conclusion of Participation assessment

and indicate the reason for study withdrawal. Ensure the Visit Status data form indicates the

type of visit is a “Premature Withdrawal visit”.

Premature Withdrawal Visit – Activity Exceptions:

•

•

•

•

•

Blood and urine research sample collection – only if not done in the last 3 months

Lumbar puncture for collection of CSF – only if not done in the last 3 months

Skin biopsy – only if not done in the last 6 months

MRI – only if not done in the last 6 months

DaTscan Imaging – only if not done in the last 6 months

1

0.6 Unscheduled Visits

An unscheduled visit may be performed only if required (i.e., deemed necessary to follow up

on adverse events, or deemed clinically relevant by the site Investigator to ensure the safety

of the participant). The following activities will be completed:

•

•

•

•

•

•

Vital signs

*Neurological examination

*Blood sample for clinical laboratory assessments

Review of current medical conditions

Review of concomitant medications

Review of adverse events

*

Conducted only if clinically indicated

1

0.7 Out of Clinic Annual Visits

To enable continued involvement of participants in the PPMI Clinical study and enhance

study retention, participants who are unable to attend annual visits in person due to reasons

such as participant burden, advanced disease, and/or participant safety (e.g., such as COVID-

1

9), may be eligible for assessment out of the clinic. Permission to have an out of clinic visit

must be obtained in advance from the PPMI Executive Steering Committee, or designee,

who will determine participant’s eligibility to participate via remotely completed

assessments. This permission may be applied to the study more broadly or PPMI sites will

notify the Site Management Core about a participant’s inability to present for an in-person

clinic visit. The site will be informed of any decision made regarding Out of Clinic visits and

will determine the appropriate approach for conducting this visit. Options for Out of Clinic

visits include virtual visits by video link (i.e., telemedicine), enhanced telephone,

PPMI

Page 27 of 55

Version Date: 01Feb2021

[figure not shown]

DocuSign Envelope ID: 706F2DD8-8346-4731-A419-FF8E7C48DF97

phone/audio only, or in-home assessments in which PPMI site staff travel to the participant’s

home. Sites should complete as many assessments indicated for the scheduled annual visit

as is feasible, based on the type of out of clinic visit conducted and ability to do an assessment

(i.e., videoconference versus in-home or audio only). Ensure the Visit Status data form

indicates the type of visit is an “Out of Clinic visit”.

1

1

2

CLINICAL ASSESSMENTS

Refer to the PPMI Assessments and eCRF Completion Manual for a detailed

description of the clinical assessments and instructions for administration.

1

SAFETY ASSESSMENTS

1

2.1 Medical Conditions Review, Physical and Neurological Examination

Medical and family history, as well as a complete physical and neurological exam will be

captured on all participants according to the schedule of activities. A neurological exam will

also be conducted annually, as well as at the last completed visit if possible.

1

2.2 Vital Signs/Weight/Height

Pulse rate (supine and standing), blood pressure (supine and standing), and oral temperature

will be determined at every visit. The supine blood pressure and pulse rate will be determined

after 1-3 minutes of quiet rest and the standing pressure and rate will be determined after 1-

3

minutes in the standing position. Weight and height will also be collected at baseline and

annually.

1

2.3 Clinical Laboratory Tests

Routine clinical safety laboratory tests indicated in the table below will be performed at the

first visit only for new enrollments (i.e., Screening for PD and Healthy Controls, Baseline

for Prodromal participants). A central laboratory will be implemented in order to conduct

identical analysis methods and utilize consistent normal ranges and thus common

interpretation of laboratory changes. If not stated otherwise, venous whole blood will be

collected in blood collection tubes (vacutainers). All samples for laboratory analysis must

be collected, prepared, labelled, and shipped according to the laboratory’s requirement as

detailed in the lab manual. The total amount of blood needed for the clinical safety lab tests

will be no more than 5 ml. No more than 60 ml will be drawn at either the Screening or

Baseline visit, including both safety and research blood samples.

The coagulation panel (PT/PTT) will be collected and shipped by all sites to the central lab

for analysis for the first visit only for new enrollments (i.e., Screening for PD and Healthy

Controls, Baseline for Prodromal participants). Sites have the option, per clinical practice,

to collect an additional blood sample to evaluate coagulation results prior to the conduct of

post Baseline Visit lumbar puncture assessments. The sample should be sent to a local lab

facility for analysis. Results will be evaluated to determine, in the opinion of the Investigator,

whether there are any issues that may preclude conduct of the follow up lumbar puncture.

Results should be maintained as part of the participant’s study documents; however, will not

be included in the study database.

PPMI

Page 28 of 55

Version Date: 01Feb2021

[figure not shown]

[figure not shown]

DocuSign Envelope ID: 706F2DD8-8346-4731-A419-FF8E7C48DF97

CENTRAL LAB TESTS

METABOLIC PANEL COMPLETE BLOOD COUNT

Sodium (Na)

Potassium (K)

Chloride (Cl)

White Blood Cell Count (WBC)

Red Blood Cell Count (RBC)

Hemoglobin (Hb)

Carbon Dioxide (CO2)

Blood Urea Nitrogen (BUN)

Glucose

Hematocrit (HCT)

Platelet Count (PLT)

Calcium (Ca)

Creatinine (Crn)

Bilirubin Total

Albumin

Total Protein

Aspartate aminotransferase (AST)

Alanine aminotransferase (ALT)

Alkaline Phosphatase (ALKP)

Uric Acid

Prothrombin time (PT) – Screening Only

Partial Thromboplastin Time (PTT) – Screening Only

1

3

BIOLOGIC RESEARCH SAMPLING

Refer to the PPMI Biologics Manual for the detailed description of the biologic samples

collected and processing instructions.

1

3.1 Blood Samples

Whole blood (about 10 ml), serum (about 30 ml) and plasma (about 10 ml) will be collected

to conduct proteomic, metabolomic, genetic and other research analyses. No more than 60

ml will be drawn at any visit, including both clinical safety labs and research blood samples.

It is strongly advised that the research blood samples are collected in a fasted state (i.e.,

minimum of 8 hours since last meal/food intake) to ensure the quality of samples for

future analyses. If fasting is not possible, then participants should be advised to eat a low

lipid diet. All research samples will be sent to a central biorepository to be stored indefinitely

for research purposes. Samples will be made available to researchers to conduct analyses

related to PD and other disorders. Participants will not receive any individual results of

research analysis or testing conducted on the biologic samples.

1

3.2 Urine

Urine (about 10 ml) will be collected to conduct analyte analyses.

1

3.3 Lumbar Puncture / Cerebral Spinal Fluid (CSF)

The lumbar puncture (LP) is performed by the site investigator or another qualified clinician

appointed by the investigator. A lumbar puncture for the collection of 15-20 ml of CSF will

be conducted for all participants per the visit schedule unless there is evidence of clinically

significant coagulopathy or thrombocytopenia that would interfere with the safe conduct of

the procedure. The first 2 ml of CSF will be processed for cell count, protein, and glucose

levels. Participants will be closely monitored the day of the procedure for adverse events.

PPMI

Page 29 of 55

Version Date: 01Feb2021

[figure not shown]

[figure not shown]

DocuSign Envelope ID: 706F2DD8-8346-4731-A419-FF8E7C48DF97

Participants will be also be contacted by phone 2 to 3 [business/working] days following an

LP to assess for any adverse events. The CSF samples will be sent to a central biorepository

to be stored indefinitely for research purposes. The CSF samples will be made available to

researchers to conduct analyses related to PD and other disorders.

1

3.4 Skin Biopsy

The skin biopsy is performed by the site investigator or another qualified clinician appointed

by the investigator. Skin punch biopsy will be performed under local anesthesia (lidocaine)

in the posterior neck according to the Schedule of Activities. Up to two punches will be

completed and the skin samples will be processed as described in the PPMI Biologics Manual

and shipped to the central biorepository for storage and analysis. Remaining samples may be

used to evaluate other proteins, analytes or potential biomarkers. Participants will not receive

any individual results of analysis or testing conducted on the skin samples. Participants will

be monitored the day of the procedure for adverse events. Participants will be also be

contacted by phone 2 to 3 [business/working] days following a skin biopsy to assess for any

adverse events.

1

4

IMAGING

1

4.1 Dopamine Transporter SPECT Imaging

Refer to the PPMI SPECT Technical Operations manual for a detailed description of

the SPECT imaging procedures.

Participants will undergo dopamine transporter imaging to measure dopamine transporter

binding using single photon emission computed tomography (SPECT). All new participants

will undergo DaTscan imaging at Screening. All new and transitioning participants will also

undergo follow up DaTscan imaging as indicated in their cohort visit schedule.

To lessen participant burden, a participant’s previously acquired DaTscan may be used in

place of a newly acquired scan as long as the previous scan was acquired within 6 months

of the study scheduled DaTscan, it meets protocol acquisition standards, and passes QC

requirements for the research study analysis.

The DaTscan imaging procedure will be performed at the individual sites using DaTscan^TM^

to target the dopamine transporter and all imaging data will be submitted for analysis to the

Imaging core. DaTscan imaging eligibility will be determined using pre-specified imaging

cut-offs. DaTscan eligibility result will be made available to the participant’s clinical site.

Women of childbearing potential must have a urine (or serum if required by the site)

pregnancy test prior to injection of DaTscan^TM^. The result must be confirmed as negative

prior to proceeding with the injection. Before the DaTscan^TM^ injection, participants will be

pre-treated with stable iodine (10 drops of a saturated solution of potassium iodide) to reduce

the uptake of DaTscan^TM^ by the thyroid. If the participant is allergic to iodine, then potassium

perchlorate 400 mg) can be substituted for potassium iodide. Participants will be injected

with up to 5 mCi of DaTscan^TM^. Within a 4-hour (+/- 30 minute) window following the

PPMI

Page 30 of 55

Version Date: 01Feb2021

[figure not shown]

[figure not shown]

DocuSign Envelope ID: 706F2DD8-8346-4731-A419-FF8E7C48DF97

injection, participants will undergo DaTscan imaging for approximately 30 minutes (or up

to an hour if the participant moved during scanning).

Participants will be monitored by study personnel for adverse events on the day that a

dopamine transporter SPECT scan is obtained. Participants will also be contacted by phone

2

to 3 [business/working] days following the injection/scan to assess adverse events.

The product used to complete the dopamine transporter SPECT scans is being used “off-

label” in the PPMI Clinical study. The imaging result obtained from the scan is not intended

to provide information about a clinical diagnosis and will not be shared with participants.

1

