progression across the spectrum of disease from prodromal PD to more advanced disease.

In PPMI Clinical, established tools will also be further validated and new technologies

including neuroimaging modalities, digital biomarkers, biochemical markers in the CSF and

plasma, genetic markers, and early clinical disease markers will be investigated. We will

continue to standardize biomarker acquisition and assessment and to establish well-defined

quantitative biomarker outcomes that are consistent among many research sites and

laboratories. Core laboratories for biomarker analysis will be used for uniformity of analyses

and quality control. A major focus of this biomarker consortium will be to extend PPMI

infrastructure to new biomarkers and new cohorts, particularly those with prodromal PD.

Longitudinal data will include participant reported outcomes with an emphasis on \outcomes

that reflect participant function throughout the course of PD

This approach to biomarker development is ambitious and requires collaboration among

many in academics, industry, government, and the public sector. However, PPMI has

demonstrated that such an approach is feasible. PPMI has been successful in providing open

source data and fostering effective collaboration. The unmet need for therapeutics that slow

or prevent the disability of PD coupled with the enormous value of biomarkers to enable and

accelerate clinical studies highlights the need for this strategy to identify and validate

biomarkers of PD progression throughout the course of disease.

4

STUDY DESIGN

PPMI Clinical is a longitudinal, observational, multi-center natural history study to assess

progression of clinical features, digital outcomes, and imaging, biologic and genetic markers

of PD progression in study participants with PD diagnosis (including patients with a LRRK2,

GBA, SNCA or rare genetic variants and individuals with prodromal Parkinson disease

(including individuals with RBD, olfactory deficit, LRRK2, GBA, SNCA or rare genetic

PPMI

Page 10 of 55

Version Date: 01Feb2021

[figure not shown]

DocuSign Envelope ID: 706F2DD8-8346-4731-A419-FF8E7C48DF97

mutations (such as Parkin or Pink1) and/or other risk factors for PD with and without DAT

deficit and healthy controls.

All participants will be comprehensively assessed for a minimum of 5 years. Participants will

undergo clinical (motor, neuropsychiatric and cognitive) and imaging assessments, and will

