GBA, SNCA, or rare genetic variants would be referred back to the study site, or another

study site, and further assessed for eligibility to enroll in PPMI Clinical.

7

PARTICIPANT ELIGIBLITY

7

.1 Healthy Controls (HC)

Note: Active Healthy controls previously enrolled in PPMI do not require re-assessment of

eligibility criteria listed below for enrollment in PPMI Clinical. Active participants do need

to be able to provide informed consent for PPMI Clinical participation (includes use of a

designated research proxy).

7

.1.1. Inclusion Criteria (HC)

a) Male or female age 30 years or older at Screening visit.

b) Individuals taking any of the following drugs: alpha methyldopa, methylphenidate,

amphetamine derivatives or modafinil, must be willing and medically able to hold the

medication for at least 5 half-lives before DaTscan imaging.

c) Confirmation that participant is eligible based on Screening DaTscan imaging.

d) Able to provide informed consent.

e) Either is male, or is female and meets additional criteria below, as applicable:

•

Female of childbearing potential who is not pregnant, lactating, or planning

pregnancy during the study and has a negative pregnancy test on day of Screening

DaTscan imaging test prior to injection of DaTscan^TM^.

PPMI

Version Date: 01Feb2021

Page 13 of 55

[figure not shown]

[figure not shown]

DocuSign Envelope ID: 706F2DD8-8346-4731-A419-FF8E7C48DF97

7

.1.2. Exclusion Criteria (HC)

a) First degree relative with PD (i.e., biologic parent, sibling, child).

b) Current or active clinically significant neurological disorder (in the opinion of the

Investigator).

c) Previously obtained MRI scan with evidence of clinically significant neurological

disorder (in the opinion of the Investigator).

d) Received any of the following drugs: dopamine receptor blockers (neuroleptics),

metoclopramide and reserpine within 6 months of Screening visit.

e) Current treatment with anticoagulants (e.g., coumadin, heparin, oral thrombin

inhibitors) that might preclude safe completion of the lumbar puncture.

f) Condition that precludes the safe performance of routine lumbar puncture, such as

prohibitive lumbar spinal disease, bleeding diathesis, or clinically significant

coagulopathy or thrombocytopenia.

g) Any other medical or psychiatric condition or lab abnormality, which in the opinion of

the investigator might preclude participation.

7

.2 Parkinson Disease (PD)

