0.1 Active PPMI Transitioning Participants

Refer to the PPMI Schedule of Activities for the applicable cohort to determine the

activities to be conducted at each visit. Participants will continue from their original

PPMI study schedule into the next planned study visit under this protocol. Note that

additional “Transition Activities” must be completed as outlined in the Schedule of

Activities for all participants transitioning into this protocol at their first in-person

visit.

Active participants previously enrolled in PPMI will not require a Screening or Baseline

visit. Participants who agree to continue participation and transition into PPMI Clinical will

enroll into PPMI and complete the next planned study visit based on the last completed visit

in PPMI (or based on timing of site activation and participant’s visit schedule). The process

of obtaining informed consent, including an explanation of study activities, is described in

the cohort visits below and will be conducted prior to completing any PPMI Clinical study

PPMI

Page 22 of 55

Version Date: 01Feb2021

[figure not shown]

[figure not shown]

DocuSign Envelope ID: 706F2DD8-8346-4731-A419-FF8E7C48DF97

activities. Participants transitioned into PPMI Clinical will be followed for a minimum of 5

years, either in person or remotely according to the respective cohort’s schedule of activities.

Active PPMI participants choosing not to continue into PPMI Clinical protocol will be

tagged by the site as “Complete”.

1

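### The pre-injection rule in 14.1 requires a negative pregnancy test but no check for lactation, although all five cohort groups bar lactating women at entry

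*Protocol*

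**What the plan says.** Section 14.1 sets the condition for injection in women of childbearing potential. The requirement begins "Women of childbearing potential must have a urine (or serum if required by the site", the test being for pregnancy, and of its outcome the section says "The result must be confirmed as negative" before the injection goes ahead. The rule is not limited to one visit. According to the same section, new participants "will undergo DaTscan imaging at Screening. All new and transitioning participants will also" have follow-up scans according to their cohort's schedule. For procedural detail the section refers to a manual: "Refer to the PPMI SPECT Technical Operations manual for a detailed description of" the imaging procedures.

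The entry criteria in 7.1.1(e), 7.2.1(i), 7.3.1(i), 7.4.1(i) and 7.5.1(e) share one wording, which begins "Female of childbearing potential who is not pregnant, lactating, or planning". They also require a negative pregnancy test on the day of the Screening scan.

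Participants already active in the original study are outside those criteria. The note in 7.1 begins "Note: Active Healthy controls previously enrolled in PPMI do not require re-assessment of" the eligibility criteria, and 7.2 to 7.5 carry matching notes. Section 10.1 adds: "Active participants previously enrolled in PPMI will not require a Screening or Baseline" visit.

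**The concern.** A pregnancy test does not detect lactation. A woman who gave birth after entry and is breast-feeding can have a negative test, and so meet the only reproductive condition that 14.1 states. The same protocol would have refused her at entry.

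The protocol itself makes the case foreseeable. Section 4 says "All participants will be comprehensively assessed for a minimum of 5 years". The healthy control, PD and PD genetic cohorts admit participants from age 30, and section 24 lists pregnancy among the events that may occur during follow-up. No visible text stops follow-up scans after a birth.

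What is at stake is participant safety and a consistent rule for sites. No estimate, comparison or objective depends on it.

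**Working it through.** No arithmetic applies, so the check sets the provisions side by side.

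| Place in Protocol | Whom and when it governs | Pregnancy | Lactation |
|---|---|---|---|
| 7.1.1(e), 7.2.1(i), 7.3.1(i), 7.4.1(i), 7.5.1(e) | New participants, at entry | Not pregnant, not planning it, negative test on day of Screening scan | Barred in 5 of 5 cohort groups |
| 14.1 | New participants at Screening; new and transitioning participants at follow-up | Negative test before injection | Not mentioned |
| Notes in 7.1 to 7.5, and 10.1 | Transitioning participants | Section 7 criteria not re-assessed | Section 7 criteria not re-assessed |
| 15.3 | Risks of DaTscan | Embryo, fetus and future offspring; pregnancy reporting | Not mentioned |
| 18.1 | Concomitant medication | Not addressed | Not addressed |

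1. *New participants.* The lactation bar is an eligibility criterion and is applied once, at entry. From then on, 14.1 is the only visible reproductive condition before an injection.

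2. *Transitioning participants.* They are not re-assessed against section 7 and have no Screening or Baseline visit. The lactation bar is therefore not applied to them at any point under this protocol. Whether they met a similar criterion in the original study is not in the text at hand.

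3. *Scans outside the usual schedule.* Section 10.3.4 adds a DaTscan when a diagnostic visit replaces an annual visit. Section 10.5 allows one at a withdrawal visit if none was done in the previous 6 months. Both fall under 14.1. The diagnostic-visit route concerns prodromal participants only, and newly enrolled ones must be 60 or older unless they carry SNCA or a rare variant.

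4. *How the other DaTscan-related entry conditions are treated.* The entry criteria require certain drugs to be held for 5 half-lives before imaging, and 18.1 repeats that for any DaTscan injection. The entry pregnancy test is repeated in 14.1. Lactation is the one present-state reproductive condition at entry that is not carried forward, and no reason is given. This looks more like an omission than a choice.

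5. *Size.* The number affected is the number of women lactating on the day of a follow-up scan. The text gives neither the sex and age distribution of the cohorts, nor the ages of transitioning participants, nor (because the schedules are figures not shown) the timing of follow-up scans. Enrolment ceilings include men and women past childbearing age, so they do not measure exposure.

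**The case against.** The strongest reply is that the check may exist where we cannot see it. Section 14.1 defers imaging detail to the SPECT Technical Operations manual, the schedules of activities are not shown, and section 24 sends significant events to the Operations Manual. A pre-injection checklist could sit in any of these. This stands as a limit on the conclusion and is why the fix is conditional. It does not remove the point. The protocol chose to state the pregnancy half of the rule in its own text, and a site reading 14.1 could take that condition as complete.

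A reader might infer that 14.1 authorises injection of a lactating woman, or that the protocol contradicts itself. The text supports neither. A negative test is written as a necessary condition. Nothing says that it is sufficient or that it overrides the investigator's judgement. An entry criterion can be wider than a later procedural check without contradiction. The gap is that no visible rule prevents the injection.

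A reader might also infer a known hazard to a breast-fed infant. The protocol states none, and gives no reason for the lactation criterion. The argument rests only on the follow-up rule being narrower than the protocol's own entry rule.

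Other provisions narrow the route. New women must not be planning pregnancy, pregnancies are captured in the database, and the investigator may withdraw a participant at any time. These make an unnoticed case less likely, but none is a lactation check. If the phrase about the study period in the entry criterion were read as covering lactation too, it would still be an eligibility criterion with no later check attached.

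**Conclusion.** The point holds as a cheap improvement of low severity. As far as the text at hand shows, the pre-injection rule for follow-up scans omits a condition that the protocol imposes on every cohort group at entry, and transitioning participants never meet that condition under this protocol. Very few women can be affected. The consequence is for participant safety only.

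The conclusion assumes that the SPECT manual, the Operations Manual and the visit schedules do not already contain a lactation check. If one of them does, what remains is a missing cross-reference in 14.1.

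**What to change.** In 14.1, require that before every DaTscan injection a woman of childbearing potential has a negative pregnancy test and is confirmed not to be lactating, and defer the scan if she is. State that this applies to new and transitioning participants, and to scans done at diagnostic or withdrawal visits. If the SPECT manual or a visit schedule already holds the check, have 14.1 refer to it explicitly.

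Section 14.2 offers a model: a participant with a contraindication to MRI may be advised to skip a Baseline or follow-up scan and still stay in the study.

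The cost is one added condition, one question per scan, and a rare deferred or missed follow-up scan.
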